**Day 0**

**Screening**

- clinical assessment, including measurement of weight and height; referral in cases of severe malaria or danger signs;
- measurement of temperature;
- parasitological assessment;
- pregnancy test (if necessary);
- informed consent.

**Enrolment**

- treatment, first dose;
- blood sampling for genotyping.

**Optional**

- urinary test to detect antimalarial drugs;
- haemoglobin/haematocrit;
- molecular markers of drug resistance;
- in vitro test;
- antimalarial drug blood concentration.

**Day 1**

- clinical assessment; referral in cases of severe malaria or danger signs;
- measurement of axillary temperature;
- parasitological assessment in cases of severe malaria or danger signs;
- treatment, second dose or alternative treatment in case of early treatment failure.

**Day 2, Day 3**

- clinical assessment; referral in cases of severe malaria or danger signs;
- measurement of axillary temperature;
- parasitological assessment;
- treatment, third to seventh dose (until day 6) or alternative treatment in case of early treatment failure.

**Day 7, Day 14, day 21, day 28, any other day**

- clinical assessment; referral in cases of severe malaria or danger signs;
- measurement of axillary temperature;
- parasitological assessment;
- alternative treatment in cases of treatment failure;
- pregnancy test at the end of follow-up (if necessary);
- blood sampling for genotyping to distinguish between recrudescence and reinfection in cases of treatment failure after day 7.

**Optional (after day 7)**

- haemoglobin/haematocrit;
- blood sampling for molecular markers for drug resistance, antimalarial blood concentration.

Appendix 7. Case report forms

| **Case report form: follow-up day 0** | | | | | | | | | | |
| --- | --- | --- | --- | --- | --- | --- | --- | --- | --- | --- |
| Health centre name: | | | | | | | | Study number: | | |
| Locality: | | | | | | | | Patient identity number: | | |
| District: | | | | | | | | Date of visit (dd-mmm-yyyy): | | |
| Province: | | | | | | | |  | | |
| **Demographic data** | | | | | | | | | | |
| Date of birth (dd-mmm-yyyy): | | | | | or estimated age:       in:  months or  years | | | | | |
| Height (cm): | | Weight (kg): | | | Sex:  Male  Female | | | | | |
| If female, is the patient pregnant?  Yes  No  Not sure **(If yes, patient is not eligible).** | | | | | | | | | | |
| If pregnant, provide the date of the last menstrual period (dd-mmm-yyyy): | | | | | | | | | | |
| **Pre-treatment temperature** | | | | | | | | | | |
| History of fever in previous 24 h?  Yes  No | | | | | | | | | | |
| Temperature:       ºC  Axillary  Tympanic  Rectal  Oral | | | | | | | | | | |
| **Thick blood smears for** ***P. falciparum*: quantitative parasite counts and qualitative gametocyte counts** | | | | | | | | | | |
| Average number of asexual *P. falciparum* parasites/l at Day 0 H0: | | | | | | | Average number of asexual *P. falciparum* parasites/l at Day 0 H12: | | | |
| Presence of *P. falciparum* gametocytes at Day 0 H0?  Yes  No | | | | | | | Presence of *P. falciparum* gametocytes at Day 0 H0?  Yes  No | | | |
| Were species other than *P. falciparum* present?  Yes  No **(If yes, patient is not eligible).** | | | | | | | | | | |
| If yes, which species?  *P. vivax*  *P. ovale*  *P. malariae* | | | | | | | | | | |
| Has blood sample for PCR been collected?  Yes  No | | | | | | | | | | |
| **Urinary test for antimalarial drugs** | | | | | | | | | | |
| Test used: | | | | Test result:  Positive  Negative | | | | | | |
| **Prior medication** | | | | | | | | | | |
| All prior medication, including natural remedies and homeopathic medicines, taken within the previous 14 days should be reported in this section. | | | | | | | | | | |
| Has the patient taken any prior antimalarial medication?  Yes  No. If yes, please specify below. Either the date of stopping or the ‘ongoing’ box should be checked. | | | | | | | | | | |
| Medicine name (generic name) | Dates | | Ongoing  (Yes = ) | | | Total daily dose and unit (e.g. 400 mg) | | | Route of administration | Indication for use |
|  | Start: | |  | | |  | | |  |  |
| Stop: | |
|  | Start: | |  | | |  | | |  |  |
| Stop: | |
|  | Start: | |  | | |  | | |  |  |
| Stop: | |

| **Case report form: follow-up day 0 (page 2)** | | | | | |
| --- | --- | --- | --- | --- | --- |
| **Medication administration** | | | | | |
| Name(s) of antimalarial drug(s) | | Time of dose (hh:min) | Number of tablets | Did the patient vomit? | Time of vomiting (hh:min) |
|  | |  |  | Yes  No |  |
|  | |  |  | Yes  No |  |
| Name(s) of other medicine(s) |  | | | | |
|  | |  |  | Yes  No |  |
|  | |  |  | Yes  No |  |

| **Case report form: follow-up day 1** | | | | | |
| --- | --- | --- | --- | --- | --- |
| Study number: | | | | | |
| Patient identity number: | | | | | |
| Date of visit (dd-mmm-yyyy): | | | | | |
| **Clinical status** | | | | | |
| Presence of danger signs or signs of severe or complicated malaria?  Yes  No  If yes, perform thick blood smear. | | | | | |
| Temperature:       ºC  Axillary  Tympanic  Rectal  Oral | | | | | |
| **Thick blood smears for estimation of *P. falciparum* parasite counts** | | | | | |
| Average number of asexual *P. falciparum* parasites/l at Day 1 H0: | | | Average number of asexual *P. falciparum* parasites/l at Day 1 H12: | | |
| Presence of *P. falciparum* gametocytes at Day 1 H0?  Yes  No | | | Presence of *P. falciparum* gametocytes at Day 1 H12?  Yes  No | | |
| Were species other than *P. falciparum* present?  Yes  No | | | | | |
| If yes, which species?  *P. vivax*  *P. ovale*  *P. malariae* | | | | | |
| **Adverse events** | | | | | |
| Presence of an adverse event?  Yes  No | | | | | |
| If yes, name the adverse event: | | | | | |
| Is it a serious adverse event?  Yes  No. If yes, inform the sponsor. | | | | | |
| **Medication administration** | | | | | |
| Name(s) of antimalarial drug(s) | Time of dose (hh:min) | Number of tablets | | Did the patient vomit? | Time of vomiting (hh:min) |
|  |  |  | | Yes  No |  |
|  |  |  | | Yes  No |  |
| Name(s) of other medicine(s) |  | | | | |
|  |  |  | | Yes  No |  |
|  |  |  | | Yes  No |  |

| **Case report form: follow-up day 2** | | | | | |
| --- | --- | --- | --- | --- | --- |
| Study number: | | | | | |
| Patient identity number: | | | | | |
| Date of visit (dd-mmm-yyyy): | | | | | |
| **Clinical status** | | | | | |
| Presence of danger signs or signs of severe or complicated malaria?  Yes  No | | | | | |
| Temperature:       ºC  Axillary  Tympanic  Rectal  Oral | | | | | |
| **Thick blood smears for estimation of *P. falciparum* parasite counts** | | | | | |
| Average number of asexual *P. falciparum* parasites/l at Day 2 H0: | | | Average number of asexual *P. falciparum* parasites/l at Day 2 H12: | | |
| Presence of *P. falciparum* gametocytes at Day 2 H0?  Yes  No | | | Presence of *P. falciparum* gametocytes at Day 2 H12?  Yes  No | | |
| Were species other than *P. falciparum* present?  Yes  No | | | | | |
| If yes, which species?  *P. vivax*  *P. ovale*  *P. malariae* | | | | | |
| **Adverse events** | | | | | |
| Presence of an adverse event?  Yes  No | | | | | |
| If yes, name the adverse event: | | | | | |
| Is it a serious adverse event?  Yes  No. If yes, inform the sponsor. | | | | | |
| **Medication administration** | | | | | |
| Name(s) of antimalarial drug(s) | Time of dose (hh:min) | Number of tablets | | Did the patient vomit? | Time of vomiting (hh:min) |
|  |  |  | | Yes  No |  |
|  |  |  | | Yes  No |  |
| Name(s) of other medicine(s) |  | | | | |
|  |  |  | | Yes  No |  |
|  |  |  | | Yes  No |  |

| **Case report form:** **follow-up day 3** | | | | | |
| --- | --- | --- | --- | --- | --- |
| Study number: | | | | | |
| Patient identity number: | | | | | |
| Date of visit (dd-mmm-yyyy): | | | | | |
| **Clinical status** | | | | | |
| Presence of danger signs or signs of severe or complicated malaria?  Yes  No | | | | | |
| Temperature:       ºC  Axillary  Tympanic  Rectal  Oral | | | | | |
| **Thick blood smears for estimation of** ***P. falciparum* parasite counts** | | | | | |
| Average number of asexual *P. falciparum* parasites/l at Day 3 H0: | | | Average number of asexual *P. falciparum* parasites/l at Day 3 H12: | | |
| Presence of *P. falciparum* gametocytes at Day 3 H0?  Yes  No | | | Presence of *P. falciparum* gametocytes at Day 3 H12?  Yes  No | | |
| Were species other than *P. falciparum* present?  Yes  No | | | | | |
| If yes, which species?  *P. vivax*  *P. ovale*  *P. malariae* | | | | | |
| **Adverse events** | | | | | |
| Presence of an adverse event?  Yes  No | | | | | |
| If yes, name the adverse event: | | | | | |
| Is it a serious adverse event?  Yes  No. If yes, inform the sponsor. | | | | | |
| **Medication administration** | | | | | |
| Name(s) of antimalarial drug(s) | Time of dose (hh:min) | Number of tablets | | Did the patient vomit? | Time of vomiting (hh:min) |
|  |  |  | | Yes  No |  |
|  |  |  | | Yes  No |  |
| Name(s) of other medicine(s) |  | | | | |
|  |  |  | | Yes  No |  |
|  |  |  | | Yes  No |  |

| **Case report form: follow-up day 7** | | | | | |
| --- | --- | --- | --- | --- | --- |
| Study number: | | | | | |
| Patient identity number: | | | | | |
| Date of visit (dd-mmm-yyyy): | | | | | |
| **Clinical status** | | | | | |
| Presence of danger signs or signs of severe or complicated malaria?  Yes  No | | | | | |
| History of fever within previous 24 h?  Yes  No | | | | | |
| Temperature:       ºC  Axillary  Tympanic  Rectal  Oral | | | | | |
| **Thick blood smears for estimation of *P. falciparum* parasite counts** | | | | | |
| Average number of asexual *P. falciparum* parasites/l: | | | | | |
| Presence of *P. falciparum* gametocytes?  Yes  No | | | | | |
| Were species other than *P. falciparum* present?  Yes  No | | | | | |
| If yes, which species?  *P. vivax*  *P. ovale*  *P. malariae* | | | | | |
| Has a blood sample for PCR been collected?  Yes  No | | | | | |
| **Adverse events** | | | | | |
| Presence of an adverse event?  Yes  No | | | | | |
| If yes, name the adverse event: | | | | | |
| Is it a serious adverse event?  Yes  No. If yes, inform the sponsor. | | | | | |
| **Medication administration** | | | | | |
| Name(s) of antimalarial drug(s) | | Time of dose (hh:min) | Number of tablets | Did the patient vomit? | Time of vomiting (hh:min) |
|  | |  |  | Yes  No |  |
|  | |  |  | Yes  No |  |
| Name(s) of other medicine(s) |  | | | | |
|  | |  |  | Yes  No |  |
|  | |  |  | Yes  No |  |

| **Case report form: follow-up day 14** | | | | |
| --- | --- | --- | --- | --- |
| Study number: | | | | |
| Patient identity number: | | | | |
| Date of visit (dd-mmm-yyyy): | | | | |
| **Clinical status** | | | | |
| Presence of danger signs or signs of severe or complicated malaria?  Yes  No | | | | |
| History of fever within previous 24 h?  Yes  No | | | | |
| Temperature:       ºC  Axillary  Tympanic  Rectal  Oral | | | | |
| **Thick blood smears for estimation of *P. falciparum* parasite counts** | | | | |
| Average number of asexual *P. falciparum* parasites/l: | | | | |
| Presence of *P. falciparum* gametocytes?  Yes  No | | | | |
| Were species other than *P. falciparum* present?  Yes  No | | | | |
| If yes, which species?  *P. vivax*  *P. ovale*  *P. malariae* | | | | |
| Has a blood sample for PCR been collected?  Yes  No | | | | |
| **Adverse events** | | | | |
| Presence of an adverse event?  Yes  No | | | | |
| If yes, name the adverse event: | | | | |
| Is it a serious adverse event?  Yes  No. If yes, inform the sponsor. | | | | |
| **Medication administration** | | | | |
| Name(s) of antimalarial drug(s) | Time of dose (hh:min) | Number of tablets | Did the patient vomit? | Time of vomiting (hh:min) |
|  |  |  | Yes  No |  |
|  |  |  | Yes  No |  |
| Name(s) of other medicine(s) |  | | | |
|  |  |  | Yes  No |  |
|  |  |  | Yes  No |  |

| **Case report form: follow-up day 21** | | | | |
| --- | --- | --- | --- | --- |
| Study number: | | | | |
| Patient identity number: | | | | |
| Date of visit (dd-mmm-yyyy): | | | | |
| **Clinical status** | | | | |
| Presence of danger signs or signs of severe or complicated malaria?  Yes  No | | | | |
| History of fever within previous 24 h?  Yes  No | | | | |
| Temperature:       ºC  Axillary  Tympanic  Rectal  Oral | | | | |
| **Thick blood smears for estimation of *P. falciparum* parasite counts** | | | | |
| Average number of asexual *P. falciparum* parasites/l: | | | | |
| Presence of *P. falciparum* gametocytes?  Yes  No | | | | |
| Were species other than *P. falciparum* present?  Yes  No | | | | |
| If yes, which species?  *P. vivax*  *P. ovale*  *P. malariae* | | | | |
| Has a blood sample for PCR been collected?  Yes  No | | | | |
| **Adverse events** | | | | |
| Presence of an adverse event?  Yes  No | | | | |
| If yes, name the adverse event: | | | | |
| Is it a serious adverse event?  Yes  No. If yes, inform the sponsor. | | | | |
| **Medication administration** | | | | |
| Name(s) of antimalarial drug(s) | Time of dose (hh:min) | Number of tablets | Did the patient vomit? | Time of vomiting (hh:min) |
|  |  |  | Yes  No |  |
|  |  |  | Yes  No |  |
| Name(s) of other medicine(s) |  | | | |
|  |  |  | Yes  No |  |
|  |  |  | Yes  No |  |

| **Case report form: day ___( any other day that is not part of regular follow-up)** | | | | |
| --- | --- | --- | --- | --- |
| Study number: | | | | |
| Patient identity number: | | | | |
| Date of visit (dd-mmm-yyyy): | | | | |
| **Clinical status** | | | | |
| Presence of danger signs or signs of severe or complicated malaria?  Yes  No | | | | |
| History of fever within previous 24 h?  Yes  No | | | | |
| Temperature:       ºC  Axillary  Tympanic  Rectal  Oral | | | | |
| **Thick blood smears for estimation of *P. falciparum*****parasite counts** | | | | |
| Average number of asexual *P. falciparum* parasites/l: | | | | |
| Presence of *P. falciparum* gametocytes?  Yes  No | | | | |
| Were species other than *P. falciparum* present?  Yes  No | | | | |
| If yes, which species?  *P. vivax*  *P. ovale*  *P. malariae* | | | | |
| Has a blood sample for PCR been collected?  Yes  No | | | | |
| **Adverse events** | | | | |
| Presence of an adverse event?  Yes  No | | | | |
| If yes, name the adverse event: | | | | |
| Is it a serious adverse event?  Yes  No. If yes, inform the sponsor. | | | | |
| **Medication administration** | | | | |
| Name(s) of antimalarial drug(s) | Time of dose (hh:min) | Number of tablets | Did the patient vomit? | Time of vomiting (hh:min) |
|  |  |  | Yes  No |  |
|  |  |  | Yes  No |  |
| Name(s) of other medicine(s) |  | | | |
|  |  |  | Yes  No |  |
|  |  |  | Yes  No |  |

| **Case report form: follow-up day 35** | | | | |
| --- | --- | --- | --- | --- |
| Study number: | | | | |
| Patient identity number: | | | | |
| Date of visit (dd-mmm-yyyy): | | | | |
| **Clinical status** | | | | |
| Presence of danger signs or signs of severe or complicated malaria?  Yes  No | | | | |
| History of fever within previous 24 h?  Yes  No | | | | |
| Temperature:       ºC  Axillary  Tympanic  Rectal  Oral | | | | |
| **Thick blood smears for estimation of *P. falciparum* parasite counts** | | | | |
| Average number of asexual *P. falciparum* parasites/l: | | | | |
| Presence of *P. falciparum* gametocytes?  Yes  No | | | | |
| Were species other than *P. falciparum* present?  Yes  No | | | | |
| If yes, which species?  *P. vivax*  *P. ovale*  *P. malariae* | | | | |
| Has a blood sample for PCR been collected?  Yes  No | | | | |
| **Adverse events** | | | | |
| Presence of an adverse event?  Yes  No | | | | |
| If yes, name the adverse event: | | | | |
| Is it a serious adverse event?  Yes  No. If yes, inform the sponsor. | | | | |
| **Medication administration** | | | | |
| Name(s) of antimalarial drug(s) | Time of dose (hh:min) | Number of tablets | Did the patient vomit? | Time of vomiting (hh:min) |
|  |  |  | Yes  No |  |
|  |  |  | Yes  No |  |
| Name(s) of other medicine(s) |  | | | |
|  |  |  | Yes  No |  |
|  |  |  | Yes  No |  |

| **Case report form: final day of follow-up (28/42)** | | | | | | | |
| --- | --- | --- | --- | --- | --- | --- | --- |
| Study number: | | | | | | | |
| Patient identity number: | | | | | | | |
| Date of visit (dd-mmm-yyyy): | | | | | | | |
| **Clinical status** | | | | | | | |
| Presence of danger signs or signs of severe or complicated malaria?  Yes  No | | | | | | | |
| History of fever within previous 24 h?  Yes  No | | | | | | | |
| Temperature:       ºC  Axillary  Tympanic  Rectal  Oral | | | | | | | |
| **Thick blood smears for estimation of *P****.* ***falciparum* parasite counts** | | | | | | | |
| Average number of asexual *P. falciparum* parasites/l: | | | | | | | |
| Presence of *P. falciparum* gametocytes?  Yes  No | | | | | | | |
| Were species other than *P. falciparum* present?  Yes  No | | | | | | | |
| If yes, which species?  *P. vivax*  *P. ovale*  *P. malariae* | | | | | | | |
| Has a blood sample for PCR been collected?  Yes  No | | | | | | | |
| **Adverse events** | | | | | | | |
| Presence of an adverse event?  Yes  No | | | | | | | |
| If yes, name the adverse event: | | | | | | | |
| Is it a serious adverse event?  Yes  No. If yes, inform the sponsor. | | | | | | | |
| **Medication administration** | | | | | | | |
| Name(s) of antimalarial drug(s) | Time of dose (hh:min) | | Number of tablets | | Did the patient vomit? | Time of vomiting (hh:min) | |
|  |  | |  | | Yes  No |  | |
|  |  | |  | | Yes  No |  | |
| Name(s) of other medicine(s) |  | | | | | | |
|  |  |  | | | Yes  No |  | |
|  |  |  | | | Yes  No |  | |
| **Urinary analysis (pregnancy test for female patients)** | | | | | | | |
| **Patients with a positive pregnancy test must be followed up for 6–8 weeks after delivery** | | | | | | | |
| Result of pregnancy test:  Positive  Negative | | | | Date of test (dd-mmm-yyyy): | | | |
| If the patient is pregnant, follow-up of the pregnancy is required, including: clinical examination of the infant at birth and 6-8 weeks after birth. Please provide comments below. If needed fill in the serious adverse event report form: | | | | | | | |
| **Case report form: final day of follow-up (28/42) (page 2)** | | | | | | | |
| **Overall assessment** | | | | | | | |
| Outcome:  adequate clinical and parasitological response  early treatment failure  late clinical failure  late parasitological failure  lost to follow-up  withdrawn | | | | | | | |
| Outcome occurred on follow-up day:      (e.g. 1, 2, 3, 7, 14, …) | | | | | | | |
| PCR:  *P. falciparum* recrudescence  *P. falciparum* reinfection  other species  mixed with *P. falciparum* recrudescence  mixed with *P. falciparum* reinfection  unknown | | | | | | |  |
| PCR corrected results:  adequate clinical and parasitological response  early treatment failure  late clinical failure  late parasitological failure  lost to follow-up  withdrawn | | | | | | |  |
| Reason for withdrawal: | | | | | | | |
| Other comments: | | | | | | | |

Appendix 8. Serious adverse event report form

| **Serious adverse event report form** | | | |
| --- | --- | --- | --- |
| Health centre name: | | | Study number: |
| Locality: | | | Patient identity number: |
| District: | | | Date of visit (dd-mmm-yyyy): |
| Province: | | | Follow-up day: |
| **Demographic data** | | | |
| Date of birth (dd-mmm-yyyy): | | or estimated age:       in:  months or  years | |
| Height (cm): | Weight (kg): |  | |
| Sex:  Male  Female | |
| If female, is the patient pregnant?  Yes  No  Not sure | | | |
| If pregnant, provide the date of the last menstrual period (dd-mmm-yyyy): | | | |
| **Serious adverse event** | | | |
| Type of event: | | | |
| Death | | | |
| Life-threatening | | | |
| Hospitalization or prolongation of hospitalization | | | |
| Permanent disability | | | |
| Congenital anomaly or birth defect  Date of occurrence (dd-mmm-yyyy): | | | |
| Describe the serious adverse event (include all relevant laboratory results): | | | |
| Describe how the reaction was treated: | | | |

| **Serious adverse event report form (page 2)** | | | | | | | |
| --- | --- | --- | --- | --- | --- | --- | --- |
| Comments (e.g. relevant medical history, drug allergies, previous exposure to similar drugs, other laboratory data, whether reaction abated after stopping the drug, whether reaction reappeared after reintroduction): | | | | | | | |
| **Outcome** | | | | | | | |
| Recovered completely | | | | | | | |
| Not yet recovered | | | | | | | |
| Recovered with long-term consequences  If patient recovered, provide date of recovery (dd-mmm-yyyy): | | | | | | | |
| **Medicines** (list the **medicine suspected of causing** the serious adverse event as well as all **concomitant medicines**) | | | | | | | |
| Brand name, batch number, manufacturer name  (list suspected medicine first) | Daily dose | Route | | | Start date | End date | Indications for use |
|  |  |  | | |  |  |  |
|  |  |  | | |  |  |  |
|  |  |  | | |  |  |  |
|  |  |  | | |  |  |  |
|  |  |  | | |  |  |  |
| **Reporting officer** | | | | | | | |
| Name: | | | | | | | |
| Qualification: | | | | | | | |
| Address: | | | | | | | |
| Phone: | | |  | | | | |
| Fax: | | |  | | | | |
| Email: | | | | | | | |
| Signature: | | | | Date: | | | |

Appendix 9. Guidelines for analysis of results

| **End-point for day X**  **(X = 28)** | **PCR-uncorrected results** | |
| --- | --- | --- |
| **Cumulative success or failure rate (Kaplan-Meier analysis)** | **Proportion**  **(per-protocol analysis)** |
| Adequate clinical and parasitological response on day X | Success | Success |
| Early treatment failure | Failure | Failure |
| Late clinical failure before day 7 | Failure | Failure |
| Late clinical failure or late parasitological failure on or after day 7 | Failure | Failure |
| Other species infection | Censored day of infection | Excluded from analysis |
| Lost to follow-up | Censored last day of follow-up according to timetable | Excluded from analysis |
| Withdrawal and protocol violation | Censored last day of follow-up according to timetable before withdrawal or protocol violation | Excluded from analysis |

| **End-point for day X**  **(X = 28)** | **PCR-corrected results** | |
| --- | --- | --- |
| **Cumulative success or failure rate (Kaplan-Meier analysis)** | **Proportion**  **(per-protocol analysis)** |
| Adequate clinical and parasitological response at day X | Success | Success |
| Early treatment failure | Failure | Failure |
| Late clinical failure before day 7 | Failure | Failure |
| Late clinical failure or late parasitological failure on or after day 7 |  |  |
| - falciparum recrudescence* | Failure | Failure |
| - falciparum reinfection* | Censored day of reinfection | Excluded from analysis |
| - other species mixed with falciparum recrudescence | Failure | Failure |
| - other species mixed with falciparum reinfection | Censored day of reinfection | Excluded from analysis |
| - other species infection | Censored day of infection | Excluded from analysis |
| - undetermined or missing PCR | Excluded from analysis | Excluded from analysis |
| Lost to follow-up | Censored last day of follow-up according to timetable | Excluded from analysis |
| Withdrawal and protocol violation | Censored last day of follow-up according to timetable before protocol violation or withdrawal | Excluded from analysis |

* WHO. *Methods and techniques for clinical trials on antimalarial drug efficacy: genotyping to identify parasite populations*.
Geneva, World Health Organization, 2008 (<http://www.who.int/malaria/resistance>).

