### 5.2.5 Genotyping of falciparum parasites

In order to differentiate a recrudescence (same parasite strain) from a newly acquired infection (different parasite strain), a genotype analysis will be conducted. This is based on the extensive genetic diversity among the malaria parasite genes *msp1*, *msp2* and *glurp*.[[2]](#footnote-3) The genotypic profiles of pre- and post-parasite strains are compared.

In order to minimize discomfort to the patient due to repeated finger pricks, two to three drops of blood will be collected on filter paper Whatman 3MM during enrolment and each time blood smears are required according to the protocol on and after day 7.

Specimens will be labelled anonymously (study number, day of follow-up, date), kept in individual plastic bags with desiccant pouches and protected from light, humidity and extreme temperature until analysed. When these conditions cannot be achieved, for example in extremely humid environments where air-conditioning is not available, storage in a refrigerator or freezer may be considered, but great care must be taken to protect samples from frost and moisture. The techniques used are polymerase chain reaction, PCR-RFLP and sequencing. The tests will be done at the laboratory of Department of Medical Research, lower Myanmar. Paired filter papers will be used for parasite DNA extraction and genotyping only in cases of treatment failure. Unused filter papers will be destroyed immediately after the study.

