8.1 Sample size

The estimated prevalence of patients positive at day 3 after artesunate 4 mg/kg/day over 7 day in the area is 15%. At a confidence level of 95% and a precision around the estimate of 10%, a minimum of 40 must be included. With a 20% increase to allow loss to follow-up and withdrawals during the 28-day follow-up period, a number of 50 patients should be targetted in the study per site.

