8.2 Analysis of data

WHO excel programme and SPSS programme will be used for data management and analysis. Data will be analysed by two methods: the Kaplan-Meier method and per-protocol analysis. In addition to the reasons for withdrawal listed in section 3.8, patients will be considered withdrawn from the analysis if the PCR results are unclassifiable or if the results of PCR indicate that the failure is due to reinfection with *P. falciparum* or *P. vivax.*

The final analysis will include:

- a description of all patients screened and the distribution of reasons for non-inclusion in the study;
- a description of all the patients included in the study;
- the number of adverse events and serious adverse events in all the patients included in the study;
- the proportion of patients lost to follow-up or withdrawn, with 95% confidence intervals and a list of reasons for withdrawal;
- the cumulative incidence of success and failure rates at day 28, PCR-uncorrected and PCR-corrected; and
- the proportion of early treatment failure, late clinical failure, late parasitological failure and adequate clinical and parasitological response at day 28, with 95% confidence intervals, PCR-uncorrected and PCR-corrected.
- The PCT, parasite reduction rate (slope of the log-linear parasite clearance curve), the parasite reduction rate at 48 hours, and the number of patients parasite positive at day 3;
- The pharmacokinetic profile of the patients.

Guidelines on calculating the cumulative success or failure rate, the proportion of adequate clinical and parasitological response and treatment failure are given in Appendix 9.

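### Excluding late failures with undetermined or missing PCR from both PCR-corrected analyses removes failures only, and probably understates the corrected day-28 failure rate

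*Protocol*

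**What the plan says.** Section 8.2 promises "the cumulative incidence of success and failure rates at day 28, PCR-uncorrected and PCR-corrected" and refers to Appendix 9 for the calculation. Appendix 9 has one table for each version.

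- **PCR-uncorrected:** "Late clinical failure or late parasitological failure on or after day 7 | Failure | Failure". A late recurrence is a failure whatever its genotype.
- **PCR-corrected:** late failures on or after day 7 are split by genotype. Recrudescence is a failure. For reinfection the row is "falciparum reinfection* | Censored day of reinfection | Excluded from analysis". For no usable genotype it is "undetermined or missing PCR | Excluded from analysis | Excluded from analysis". Loss to follow-up and withdrawal are censored in Kaplan-Meier and excluded in per-protocol.
- Early treatment failure, and late clinical failure before day 7, count as failures in both tables without any PCR.

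Section 5.2.5 limits who is typed: "Paired filter papers will be used for parasite DNA extraction and genotyping only in cases of treatment failure".

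Section 8.2 words the rule differently: "patients will be considered withdrawn from the analysis if the PCR results are unclassifiable". On the final-day case report form (Appendix 7), the PCR field offers unknown, but the PCR-corrected result has no undetermined or excluded option. The nearest choice is withdrawn.

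**The concern.** A PCR result can be undetermined or missing only in a patient who has already had a late recurrence. The exclusion therefore depends on the outcome: it takes possible failures out of numerator and denominator, and it never takes out a success. What remains is the failure rate among patients who either did not fail or failed with a readable genotype.

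Efficacy is part of the primary objective (section 2), and the results are meant to inform national treatment guidelines and containment. Both corrected analyses use the same rule, so agreement between Kaplan-Meier and per-protocol would not show that either is sound.

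The two statements of the rule also differ. A patient withdrawn under section 8.2 is censored in the Appendix 9 Kaplan-Meier analysis. A patient with undetermined PCR under Appendix 9 is deleted from it. Two analysts could treat the same patient differently.

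**Working it through.** **Inputs.** N = 40 and 50 are the minimum and target in section 8.1. They were set for day-3 positivity ("At a confidence level of 95% and a precision around the estimate of 10%, a minimum of 40 must be included"), so the protocol has no day-28 failure rate of its own to reproduce here. It also gives no expected number of unreadable samples. The counts below are assumptions, with no losses to follow-up.

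The recrudescent share comes from section 1. In 2007, 2 of 3 late failures on artesunate-amodiaquine and 3 of 5 on artemether-lumefantrine were recrudescent: (2+3)/(3+5) = 5/8. For the later study, section 1 read literally excludes reinfection in all 8 + 4 = 12 recurrences.

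**Notation.** R = confirmed failures, I = reinfections, U = undetermined, A = adequate responses = N − R − I − U, π = recrudescent share among the U.

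**Direction, per-protocol.** The rule gives R/(R+A). The true value is (R+πU)/(R+πU+A). The second is larger for any π > 0 and equal at π = 0.

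**Direction, Kaplan-Meier** (all recurrences on the same day). The rule gives R/(N−U). The true value is (R+πU)/N. The rule is too low when π > R/(N−U), which is the rate that it reports.

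**Scenario 1: N = 40, R = 4, I = 2, U = 2, so A = 32.**

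| Handling of the 2 undetermined | Per-protocol | Kaplan-Meier |
|---|---|---|
| Rule as written | 4/36 = 11.1% | 4/38 = 10.5% |
| All as reinfection | 4/36 = 11.1% | 4/40 = 10.0% |
| Share 5/8 recrudescent | 5.25/37.25 = 14.1% | 5.25/40 = 13.1% |
| All as failure | 6/38 = 15.8% | 6/40 = 15.0% |

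The Kaplan-Meier threshold here is 10.5%, far below 5/8. If both were reinfections, per-protocol would be right and Kaplan-Meier slightly high (10.5% against 10.0%).

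**Scenario 2: N = 50, no early failures, 5 late recurrences, all recrudescent** (1 on day 14, 2 on day 21, 2 on day 28), one day-21 sample unreadable.

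- All as failure: 5/50 = 10.0%.
- Excluded: 4/49 = 8.2%.
- Censored on the day: 1 − (49/50)(48/49)(45/47) = 8.1%.

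Censoring instead of excluding therefore cures nothing. Only the classification of the patient moves the figure.

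**Size with one unreadable sample, N = 50, no early failures, F late recurrences all recrudescent.** Relative bias = 50(F−1)/(49F) − 1:

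- F = 4: 150/196 − 1 = −23.5%
- F = 5: 200/245 − 1 = −18.4%
- F = 6: 250/294 − 1 = −15.0%
- F = 8: 350/392 − 1 = −10.7%

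**Early failures shrink this**, because they count without PCR. With 1 early and 8 late failures, all late ones recrudescent and one unreadable: (8/49)/(9/50) − 1 = 400/441 − 1 = −9.3%.

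**No confirmed failures.** With N = 40, R = 0, I = 0, U = 2, the rule reports 0%, while the rate could be up to 2/40 = 5.0%.

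**The case against.** The best case on the other side has four parts.

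**The bias is neither certain nor of known size.** A reader might infer that the rule always lowers the failure rate, that the relative bias is the same whatever the recrudescent share, or that one unreadable sample always costs more than 10% of the rate when late recurrences number 8 or fewer. The documents support none of these. The rule is harmless in per-protocol if every undetermined case is a reinfection. Per-protocol also drops known reinfections, so the share does not cancel there (N = 50, F = 8: −10.7% at a share of 1, about −11.3% at 5/8). Early failures can bring the bias below 10%. The number of unreadable samples may be zero, and the 5/8 rests on eight events under other regimens and at other sites (exact 95% interval 24 to 91%). All of this stands. Even so, the lower end of that interval is above the Kaplan-Meier threshold of 10.5% in scenario 1.

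**Deleting rather than censoring is a side issue.** A reader might see removal from day 0 in Kaplan-Meier as the main fault. The figures of 8.2% and 8.1% show that it is nearly immaterial.

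**Much is already visible.** The uncorrected rate keeps these patients as failures, and section 8.2 asks for the withdrawn proportion with reasons. A reader might also infer that the uncorrected rate is biased. Appendix 9 counts these patients there, so it is not affected by this row. But that rate counts known reinfections as failures too: in scenario 1 it is (4+2+2)/40 = 20.0%, against 15.0 to 15.8% for the corrected upper bound. It is a looser limit, not a substitute.

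**Importance is limited.** Section 5.1.1 calls the study descriptive. Day-3 positivity and the clearance measures need no PCR, no decision threshold attaches to the corrected rate, and a change from 10.0% to 8.2% lies well inside the exact 95% interval for 5/50 (3.3 to 21.8%). This stands, and limits the weight of the point. It does not justify leaving a one-sided rule without bounds.

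**Conclusion.** The point holds in a limited form. For late failures on or after day 7 without a usable PCR, Appendix 9 fixes an exclusion that depends on the outcome, in both corrected analyses. It understates the corrected day-28 failure rate in per-protocol if any of these cases are recrudescent. In Kaplan-Meier it does so if their recrudescent share exceeds roughly the failure rate reported under the rule. The protocol's own earlier data make both likely but do not prove either.

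The size is conditional on counts that the protocol does not state: 8.2% instead of 10.0% in scenario 2, and 11.1% against a possible 11.1 to 15.8% (per-protocol) in scenario 1. With no unreadable samples there is no bias.

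Separately, and without any assumption, section 8.2 and Appendix 9 give different Kaplan-Meier rules for the same patients. The point is a cheap improvement to the reporting of one result. It does not undermine the study.

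**What to change.** In the PCR-corrected part of Appendix 9, keep the planned figure and report two bounds beside it:

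1. All late failures with undetermined or missing PCR counted as failures on the day of recurrence.
2. All of them handled as reinfection: censored on that day in Kaplan-Meier, excluded in per-protocol.

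State how many such patients there are. Make section 8.2 and Appendix 9 give the same rule, and give the PCR-corrected result on the case report form an option that matches it.

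Reallocating these cases by the recrudescence share observed in this trial may be added as an optional secondary analysis. With only a handful of genotyped failures that share will be imprecise, so it should not be the headline.

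The cost is some wording and a few analysis lines, with no new samples, data or patients. The planned figure stays, so comparability with other studies using the same convention is kept. The only downside is a less favourable upper bound on failure.
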